# Effectiveness of lumbar stabilization exercise with real-time ultrasound imaging biofeedback on lumbar multifidus muscle cross-sectional area in individuals with non-specific chronic low back pain: a study protocol for a randomized controlled trial

**DOI:** 10.1186/s13063-021-05952-9

**Published:** 2022-01-06

**Keywords:** Chronic low back pain, Lumbar stabilization exercise, Lumbar multifidus muscle, Cross-sectional area, Pain, Functional disability, Real-time ultrasound imaging biofeedback, Quality of life

## Abstract

**Background:**

Structural impairment of the lumbar multifidus muscle, such as reduced cross-sectional area, is evident among individuals with chronic low back pain. Real-time ultrasound imaging (RUSI) biofeedback has been reported to improve preferential activation of as well as retention in the ability to activate the lumbar multifidus muscle during lumbar stabilization exercises (LSE). However, evidence of the effectiveness of this treatment approach in individuals with non-specific chronic low back pain (NCLBP) is still limited. The purpose of this study is, therefore, to determine the effectiveness of LSE with RUSI biofeedback on lumbar multifidus muscle cross-sectional area in individuals with NCLBP.

**Methods/Design:**

This study is a prospective, single-center, assessor-blind, three-arm, parallel randomized controlled trial to be conducted at National Orthopedic Hospital, Kano State, Nigeria. Ninety individuals with NCLBP will be randomized in a 1:1:1: ratio to receive LSE, LSE with RUSI biofeedback, or minimal intervention. All participants will receive treatment twice weekly for 8 weeks. The primary outcome will be the lumbar multifidus muscle cross-sectional area. The secondary outcomes will include pain (Numerical Pain Rating Scale), functional disability (Roland–Morris Disability Questionnaire), and quality of life (12-Item Short-Form Health Survey). All outcomes will be assessed at baseline, 8 weeks post-intervention,  and 3 months follow-up.

**Discussion:**

To our knowledge, this study will be the first powered randomized controlled trial to compare the effectiveness of LSE training with and without RUSI biofeedback in individuals with NCLBP. The outcome of the study may provide evidence for the effectiveness of LSE with RUSI biofeedback on enhancing the recovery of the lumbar multifidus muscle in individuals with NCLBP.

**Trial registration:**

Pan African Clinical Trials Registry (PACTR201801002980602). Registered on January 16, 2018.

**Supplementary Information:**

The online version contains supplementary material available at 10.1186/s13063-021-05952-9.

## Background

Low back pain (LBP) is a common musculoskeletal disorder causing years lived with disability than any other condition around the world [1]. It is a major public health issue owing to its multifactorial impact including pain, activity limitations, participation restrictions, career burden, healthcare utilization, and huge economic costs [2, 3]. Moreover, the burden of LBP is projected to increase over the coming decades due to population increase and aging [3]. Hence, there is a need to prioritize LBP and identify effective intervention strategies to reduce the consequences of the current and projected future burden 3.

Although many sp inal structures could be claimed responsible for the origin of LBP, for up to 9 5% of cases, the specific cause of the pain cannot be reliably identified [4]. However, prior biome chanical studies suggest that impairments in the key stabilizing muscles of the spine could be attributed to the development or recurrence of subacute and non-specific chronic back complaints [5]. For example, it has been documented that structural impairments of the lumbar multifidus muscles (LMM), such as reduced cross-sectional area (CSA) [6–9], thickness [10–12], and increased fat infiltrations [7, 9, 13–15], are evident among individuals with chronic LBP. 

One treatment approach believed to be able to improve these LMM dege nerative changes is lumbar stabilization exercise (LSE) program. This specific exercise approach is commonly applied by physiotherapists to rehabilitate individuals with chronic low back disorders [16–20]. Importantly, there is evidence to support its efficacy in improving pain, functional disabil ity, and quality of life (QOL) among sufferers of chronic LBP even though it may not be superior to other types of exercise programs [21, 22].

The focus of LSE is to train the skilled activation of the deep trunk muscles particularly the LMM and transversus abdominis (TrA) muscle [23]. Improving the activation capacity of the LMM is believed to enhance its function (i.e., providing segmental stability and controlling intervertebral motion [24]) by reversing the degenerative changes commonly seen in the muscle [5]. However, to improve the precision of muscle contraction while performing LSE, it is crucial to provide accurate feedback during the training. This may involve any of the senses including tactile (palpation), auditory (electr omyography), and visual ultrasound imaging information [25]. Though the use of palpatory feedback is commonly practiced, v isual feedback using real-time ultrasound imaging (RUSI) has been shown to be promising in providing preferential activation of the deep trunk musculature during LSE in asymptomatic individuals [26, 27]. More specifically, Van et al. [27] asserted that the use of RUSI biofeedback may improve not only LMM activation performance but also retention in the ability to activate the muscle, which is crucial for individuals with LBP as reoccurrences are common [18]. Consequently, the  use of this bio feedback approach may reduce the number of trials required to consistently perform isometric contraction to activate the deep stabilizing trunk muscles [26].

Most trials examining the effectiveness of LSE on LMM CSA or thickness did not provide RUSI as biofeedback to improve LMM preferential activation or contraction quality. Although previous but small trials found LSE with RUSI to be effective at improving LMM CSA [28–30], pain, and disability [28, 29] in patients with non-specific LBP, evidence of the effectiveness of this treatment approach among patients with non-specific chronic LBP (NCLBP) is still limited due to lack of rigorous trials in the way of randomized controlled trials (RCTs). Of the four trials examining the effectiveness of LSE with RUSI on LMM CSA [28–30] or thickness [31] in patients with non-specific acute LBP [28] or NCLBP [29–31], all suffered a small sample size (*n* = 10–41) without a priori power calculation, and two were non-RCT [29, 30] of which one included  elite cricketers [30].

According to the latest systematic review [32] to summarize the evidence regarding the effectiveness of LSE on LMM morphology, very low- to low-quality evidence exists that LSE improves LMM CSA post-intervention or compared to medication, general exercise, or general physiotherapy in patients with non-specific LBP. However, only one RCT [28] (conducted among acute LBP patients) of the five included RCTs [28, 33–36] used RUSI as biofeedback. Furthermore, on the basis of two small trials [28, 37] in which one included patients with acute LBP [28] and the other included patients with  chronic LBP [37], the review [32] found no evidence to support the correlation between changes in LMM CSA  and changes in pain or disability. Thus, it is imperative to explore  if the addition of RUSI biofeedback in LSE training would provide more favorable effect on LMM CSA compared to LSE training without RUSI biofeedback, and to examine the correlation between changes in LMM CSA and LBP or LBP-related disability among individuals with NCLBP. 

Our recent pilot study [29], even though was limited to being a single-group pretest-posttest design, suggests the feasibility of conducting a large-scale RCT  to determine the efficacy of LSE with RUSI biofeedback in individuals with NCLBP. The use of LSE with RUSI biofeedback resulted in significant improvement in LMM CSA by 1.7 points, pain by 3.9 points, and  disability by  4.5 points. However, no significant improvement in  physical and mental health was observed after the intervention, which could be attributed to the shorter treatment (12 sessions) provided [29]. Thus, the purpose of this study is to determine the effectiveness of LSE with RUSI biofeedback in individuals with NCLBP. The primary outcome will be LMM CSA whereas the secondary outcomes include  pain, functional disability, and QOL. 

## Methods/Design

### Hypothesis 

We hypothesized that patients receiving LSE with RUSI biofeedback will demonstrate significant improvement in LMM CSA, pain, functional disability, and QOL compared to those receiving LSE without RUSI biofeedback or minimal intervention (control). 

### Primary objective

To determine the effectiveness of LSE with RUSI biofeedback on LMM CSA in individuals with NCLBP.

### Secondary objectives 

To determine the effec tiveness of LSE with RUSI biofeedback on pain, functional disability, and QOL in individuals with NCLBP. Additionally, we will determine the association between  post-treatment scores in LMM CSA and post-treatment scores in pain and functional disability.  

### Study design 

This study will be a prospective, single-center, assessor-blind, three-arm, parallel RCT and will be conducted at the Physiotherapy Department, National Orthopedic Hospital, Dala, Kano State, Nigeria. The outline of the study is presented in Fig. 1. The protocol for this study is reported in accordance with the Standard Protocol Items: Recommendations for Interventional Trials (SPIRIT) 2013 Checklist (Additional file 1).

**Fig. 1 Fig1:**
[figure not shown]
Flow of participants through the study

### Physiotherapists/research assistants

The principal investigator (RS) and two physiotherapists (with about 4 to 6 years of working experience in musculoskeletal physiotherapy)  will be responsible for patients’ screening, appointment, and treatment. A consultant radiologist (with over 10 years of experience) blinded to group allocation in diagnostic ultrasound imaging will be responsible for ultrasound imaging and measurements. Another physiotherapist (with about 3 years of working experience in musculoskeletal physiotherapy) blinded to group allocation will be responsible for the assessment of self-report questionnaires. All the physiotherapists will receive a training session and written instructions for the study protocols.

### Participants and recruitment

Patients with LBP attending outpatient physiotherapy and those referred for physiotherapy by orthopedists will be screened for their suitability to participate in the study. Participants’ eligibility will be ensured through history taking and physical examinations. The participants will be included if they (1) are male or female between the age of 18 and 60 years, (2) have a primary complaint of non-specific LBP with or without leg pain for 12 weeks or more, and (3) are able to read and understand Hausa or English language or both. Part icipants will be excluded if they (1) have a history of spine surgery; (2) have obvious deformities affecting the trunk or upper and lower extremities; (3) have serious spinal pathology such as infection, fracture, metastases, and cauda equine syndrome; (4) have a history of medical or surgical conditions that might hinder exercise performance; and (5) are pregnant or lactating women. Participants meeting the eligibility criteria and who accept willingly to participate will be given oral and written information about the study procedures. They will also be informed about their rights to withdraw from participation at any time without prejudice. Informed consent will be obtained via signature or thumbprint.  Participants’ baseline demographic and clinical variables, such as age, gender, marital status, education level, employment status, pain duration, height, weight, and body mass index will be collected and recorded after group allocation. The participants will be identified only by their initials using  research notes.

### Rando mization and blinding

A record clerk who will not be involved in the assessment and treatment of participa nts will be responsible for the random allocation of participants into different intervention groups. The participants will be randomly assigned into LSE group, LSE with RUSI biofeedback (LSER) group,  or minimal in tervention (control) group in a 1:1:1 ratio (i.e., 30 participants per group) (Fig. 1). Consecu tively numbered (1 to  90) sealed opaque envelopes will be prepared using a computer-generated randomization sequence with permuted blocks of varying sizes (i.e., 3 and  6) by an independent statistician. Once a participant fulfilled the inclusion criteria and give consent for the study, the record clerk will perform the randomization by picking a sequential envelope and assign the participant to the group written in the envelope. All assessors will be blinded to participants’ group allocation. However, because of the nature of the interventions, it will be difficult to blind the participants and investigators (physiotherapists) to treatment allocation. Unbinding conditions will not occur but maybe only permissible when there is a medical emergency.

### Outcome assessment

Primary outcome will be LMM CSA assessed with RUSI whereas secondary outcomes will include pain, functional disability, and QOL to be assessed using self-report questionnaires. All outcomes will be assessed at baseline (−*t*_*1*_), 8 weeks post-intervention (*t*_*2*_), and 3 months follow-up (*t*_*3*_) (Table 1).

**Table 1 Tab1:**
[figure not shown]
SPIRIT figure: time points for en rollment, interventions, and assessment

#### Lumbar multifidus muscle cross-sectional area

The procedure for the LMM CSA will be identical to that described in previous studies [30, 38]. We found a within-day assessor intra-rater reliability during our pilot trial (*n* = 10) [29] to be excellent (intraclass correlation coefficients = 0.96) similar to findings of previous studies [39, 40]. Also, LMM CSA measurements obtained using RUSI have been validated by comparison with magnetic resonance imaging measurements [40]. The imaging of the LMM CSA will be measured at the L5 level using real-time ultrasound apparatus (Edan D3 version 1.6, China) with a 5-MHz curvilinear transducer. Participants will be placed on prone lying, on a plinth with arms by their sides and head turned to a preferred side. To keep the lumbar spine in a neutral position, a pillow will be placed under the hips to make the lower lumbar spine flat. The L5 spinous process will be identified by palpation, and the skin will be marked using a pen for reference. An acoustic coupling gel will be applied to the skin and the transducer head. Thereafter, the transducer head will be placed longitudinally along the midline of the lumbar spine to confirm the L5 level. The transducer head will be then placed transversely over the spinous process of L5 to obtain imaging of the spinous process and laminae along with the LMM on both sides of the spine. Transverse images of the LMM will be obtained bilaterally with the small side (thinner) being considered as the LMM CSA of the patient. Measurements will be taken during maximal voluntary isometric contraction. To ensure accuracy, average measures of three images of the LMM will be taken. The L5 level is chosen in this study because previous studies indicate that decreased LMM CSA and increased side-to-side asymmetry are common at this level [30, 41].

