#### Lumbar stabilization exercise with real-time ultrasound imaging biofeedback (LSER)

Herein, the intervention will be similar to that described in the LSE group except for the addition of RUSI biofeedback to enhance the precision of contraction and activation performance of the LMM. While maintaining a neutral spine in prone lying, the transducer head of the ultrasound will be placed transversely over the L2–L5 levels and then the participants will be instructed to perform isometric contraction of the LMM and other deep stability muscles as described above. Specifically, they will be instructed to focus on the monitor to see the changes in the thickness of the LMM as they contract the muscles and put in their best effort to increase the thickness with successive contractions. Contractions will be held for 10 s and repeated 10 times, with a period of 30- to 60-s rest between repetitions.

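### The head position allowed at the primary ultrasound scan does not rule out screen feedback during a test that closely resembles the LSER training task

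*Protocol article*

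**What the plan says.** The outcome section on multifidus CSA describes the scan in some detail. On the device and level: "The imaging of the LMM CSA will be measured at the L5 level using real-time ultrasound apparatus". On posture: "Participants will be placed on prone lying, on a plinth with arms by their sides and head turned to a preferred side". On the state of the muscle: "Measurements will be taken during maximal voluntary isometric contraction". On replication: "To ensure accuracy, average measures of three images of the LMM will be taken". The same section sets the pillow, the skin mark, the gel and the transducer orientation, and refers the procedure to two cited studies.

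The LSER intervention section describes training with the participant prone, spine neutral and transducer transverse over the lumbar levels. During this, "they will be instructed to focus on the monitor to see the changes in the thickness of the LMM as they contract the muscles", with best effort to increase thickness over successive contractions. The Interventions section sets two sessions a week for 8 weeks, so up to 2 × 8 = 16 sessions. The LSE arm practises the same contraction without the image.

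On blinding, the staffing section says that a consultant radiologist, blinded to allocation, "will be responsible for ultrasound imaging and measurements". The randomization section adds: "All assessors will be blinded to participants’ group allocation". It also concedes that participants and treating physiotherapists can hardly be blinded.

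**The concern.** The randomized difference between LSER and LSE is sight of the ultrasound image during contraction. The primary outcome is measured under ultrasound, prone, during a voluntary contraction, and so depends on effort and skill. If the image is visible at the test, the ingredient under study is present while its effect is measured, and only one arm has been taught to use it.

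The Background section rests the case for biofeedback on two things: better activation, and retention of the ability to activate the muscle. A scan taken with feedback available shows what participants can do with feedback. A scan taken without it shows what they have kept. The two cannot be separated afterwards if screen visibility was neither controlled nor recorded. At stake is the interpretation of the LSER–LSE contrast on the primary outcome.

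**Working it through.** **1. Training and test side by side**

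| Feature | LSER training | Primary outcome scan |
|---|---|---|
| Posture | Prone, spine neutral | Prone, pillow under hips, spine neutral |
| Transducer | Transverse, L2–L5 | Transverse, L5 |
| Muscle | Isometric contraction, best effort to increase thickness | Maximal voluntary isometric contraction |
| Image | Participant told to watch it | Not stated whether visible |
| Head | Must allow sight of the monitor | Side chosen by the participant |

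The two set-ups differ in what is read (thickness as the training cue, CSA as the outcome) and in what is said about the screen. The outcome section does give a rule for the head, and that rule allows either side. It does not require the same side at each visit.

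**2. Which contrast would be affected**

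Outcomes are assessed at baseline, 8 weeks and 3 months. At baseline no arm has trained, so any help from the screen should be similar across arms. At the two later visits only LSER has practised using the image. An advantage from seeing it would therefore enter the group-by-time term and the LSER–LSE difference, in the same place as a true treatment effect. The direction follows from the article's own premise that visual feedback improves activation, plus the assumption that stronger activation enlarges the measured CSA.

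**3. Scale, from assumed inputs**

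The article gives no figure for a feedback gain. It does give a yardstick in the Sample size calculations section: a target of 1.0 point between LSER and LSE, SD 2.5, f = 0.32, correlation 0.5, power 85%, N = 75.

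That N reproduces. For the between-groups effect with three groups and three measurements, λ = f²·N·m/(1 + (m − 1)ρ) = 0.32² × 75 × 3/(1 + 2 × 0.5) = 11.52 on 2 and 72 degrees of freedom, which gives power 0.854. N plays no further part here except as 75/3 = 25 evaluable per arm.

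Let b be the average shift in LSER caused by seeing the screen, with no true effect. In a simple two-sample normal comparison, SE = 2.5 × √(2/n), which is 0.707 for n = 25 and 0.645 for n = 30. The two-sided 5% rejection probability is 1 − Φ(1.96 − b/SE) + Φ(−1.96 − b/SE):

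| Assumed b (points) | 25 per arm | 30 per arm |
|---|---|---|
| 0 | 5.0% | 5.0% |
| 0.25 | 6.4% | 6.7% |
| 0.5 | 10.9% | 12.1% |
| 1.0 | 29.3% | 34.1% |

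The values of b are assumptions, and the comparison is simpler than the planned mixed ANOVA with post hoc tests. The table shows how sensitive the contrast would be. It does not show that any such shift exists.

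**The case against.** The strongest reply is that the head-position clause is an ordinary comfort instruction for a prone patient. Nothing in the article places the monitor within view. Screen placement is an operational detail that a condensed article may leave to the full protocol or to the two cited procedures, neither of which is at hand. All of this stands as far as the facts go: nobody can say from the text that participants see the screen. It does not remove the point, because the article states a positioning rule, in a section that is otherwise specific, and that rule leaves open the one feature that bears on the randomized ingredient.

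A reader might also infer three stronger things, which the documents do not support:

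- **That CSA is traced live in front of the participant.** The radiologist does both the imaging and the measuring, but averaging three images is equally compatible with frames captured and measured later.
- **That LSER participants will reveal their arm to the radiologist.** This is a general possibility wherever participants know their treatment. It does not follow from the head position, and the article states that assessors are blinded. Nor does it fix the direction of any reading bias.
- **That the bias has a known size.** If a fraction q of LSER participants saw the screen and gained g, the shift would be q × g. With q = 0.5 and g = 0.2 to 0.6 this is 0.10 to 0.30 points, or 10% to 30% of the 1.0-point target. Both inputs are invented, so the result only returns what was put in.

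Finally, the screen can matter only because the measurement is made under voluntary contraction. This point therefore depends on that choice; it is not an independent fault.

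**Conclusion.** The point holds as a design weakness that is cheap to close. There is no contradiction and no wrong number. The primary scan resembles the LSER training task, and its positioning rule permits, without establishing, that trained participants watch the image while being tested. If they do, the LSER–LSE difference at 8 weeks and 3 months would be expected to shift towards LSER, and would no longer be a clean measure of retained ability. The size cannot be quantified from the documents. The conclusion rests on three assumptions: that the monitor is visible from at least one head side, that seeing it improves the contraction in those trained to use it, and that a better contraction enlarges measured CSA.

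**What to change.** In the outcome section on multifidus CSA, replace the clause that leaves the head side to the participant with wording such as: *head turned away from the ultrasound monitor, same side at every visit, with the monitor out of the participant's sight and no verbal or visual feedback on the image in any arm.* This costs one sentence and a turned or covered screen.

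As a secondary safeguard for the stated assessor blinding, ask participants not to mention their treatment. Where images are stored, have the same radiologist measure them under code, in random order, without arm or visit shown. This needs image storage and some extra reading time, but no additional staff.

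The Trial status section gives first enrollment on 1 August 2019, follow-up expected complete by 30 September 2021 and approval of the current version on 4 October 2021, so the scans may already be done. In that case, report whether the screen was visible to participants at assessment and whether the head side was kept constant, and re-measure stored images under code where they exist. Re-measurement would protect the reading, but it cannot undo feedback that was available during the contraction. If the screen was visible, that limitation should be stated beside the LSER–LSE result.

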## Discussion

Previous small RCT (*n* = 41) suggests that a 4-week LSE training with RUSI biofeedback may improve LMM CSA in patients with non-specific acute LBP compared to analgesics alone [28]. In contrast, in an RCT by Partner and colleagues [31] to compare LMM thickness in patients with NCLBP before and after a single session of LSE with and without biofeedback including the use of RUSI, no significant inter-group difference was detected for LMM thickness. Their study [31] however is underpowered, suffered a small sample size (*n* = 22), and included a single exercise session which may not be adequate to induce a significant change in the outcome observed. Taking into account  methodological limitations of these trials [28, 31], a powered RCT will be conducted to determine  the effectiveness of 8-week LSE training with RUSI biofeedback compared to LSE training without biofeedback, or minimal intervention in individuals with NCLBP. After the intervention, outcomes will be also evaluated at the 3-month follow-up and possibly at the 6-month or 12-month follow-up. If our hypothesis is correct, this study has the potential to inform  the decision to change practice by providing evidence for the clinical effectiveness of LSE with RUSI biofeedback on enhancing recovery of LMM size, which is commonly implicated in LBP and reoccurrence [5]. 

As a secondary objective, the present study will seek to examine the relationship between p ost-treatment change in LMM CSA and pain as well as disability. This may help to establish causality effect regarding LSE training with RUSI biofeedback on LM M morphology (i.e., CSA) and LBP and LBP-related disability.

This study however is without some limitations. The measurement of LMM CSA will be only performed at the L5 level even though aberrations in LMM morphology are commonly observed at this level [30, 41], besides evidence of recovery following specific rehabilitation [28, 30]. Therefore, any changes in the LMM CSA in other levels of the lumbar spine following rehabilitation could not be detected. Furthermore,  other important LMM morphological-related outcomes such as fat infiltration, volume, and percentage thickness will not be evaluated due to limited resources. Nevertheless, the planned powered, single (assessor) blind, three-arm (including comparator and active control groups), parallel RCT design is the strength of our study.  

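### The primary outcome is LMM cross-sectional area under maximal contraction, which mixes muscle size with trained activation, so it cannot by itself support a conclusion of recovered muscle size

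*Protocol article*

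**What the plan says.** **Endpoint.** Outcome assessment states: "Primary outcome will be LMM CSA assessed with RUSI". The section on LMM cross-sectional area places the participant prone, and "a pillow will be placed under the hips to make the lower lumbar spine flat". Images are taken at L5 on both sides, the smaller side counts, and three images are averaged. On the state of the muscle it says: "Measurements will be taken during maximal voluntary isometric contraction". No resting image is described in the article.

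**Training.** In the LSER section, participants lie prone in neutral spine and contract the LMM under ultrasound. They are told to "focus on the monitor to see the changes in the thickness of the LMM as they contract the muscles" and to "put in their best effort to increase the thickness with successive contractions". The biofeedback is added "to enhance the precision of contraction and activation performance of the LMM". The LSE section teaches the same isometric contraction, prone, with the same holds, repetitions and rest, but no screen. The minimal intervention is three general exercises, which all arms perform. All arms attend twice weekly for 8 weeks, i.e. 2 × 8 = 16 sessions.

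**Interpretation.** The abstract's Background begins with "Structural impairment of the lumbar multifidus muscle, such as reduced cross-sectional area". The Discussion says that, if the hypothesis is correct, the trial could provide evidence on "enhancing recovery of LMM size, which is commonly implicated in LBP and reoccurrence". It adds that the analysis relating CSA change to pain and disability may help to establish causality with respect to LMM morphology.

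**The concern.** The question is framed in structural terms, but the measurement depends on performance. A larger contracted CSA can come from a larger muscle, from a better or harder contraction, or from both. The arms differ by design in how they are trained to contract, and the declared purpose of the biofeedback is better activation. A positive result could therefore be read as regained muscle size when some of it is a learned skill. At stake is the meaning of the headline conclusion, and of the planned analysis relating CSA change to pain and disability.

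Blinding the radiologist does not address this, because the participant, who is not blinded, produces the contraction. The 3-month scan does not address it either: the Background expects biofeedback to improve retention of the ability to activate the muscle as well as activation itself. The good intra-rater reliability from the pilot concerns repeatability of reading, not what is being read.

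**Working it through.** The plan gives no figure for this point, and the sample-size calculation does not bear on it. The check is a decomposition set against the passages.

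**Step 1: what is measured.** For a participant at a given scan, write

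C = R + E

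where C is contracted CSA, R is resting CSA and E is the enlargement on maximal voluntary contraction. The protocol article describes measurement of C only.

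**Step 2: what each arm trains.** Let t be the gain in E from training the LMM contraction without a screen, and s the further gain from practising with the screen. Both are taken relative to the general exercises that all arms perform.

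| Arm | LMM contraction taught | Screen feedback | Gain in E |
|---|---|---|---|
| LSER | yes | yes | t + s |
| LSE | yes, same position and dosage | no | t |
| Control | no | no | 0 (reference) |

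**Step 3: what each contrast contains.** With D_R the between-arm difference in change of resting size and D_C that in contracted CSA:

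- LSER − LSE: D_C = D_R + (t + s) − t = D_R + s
- LSER − control: D_C = D_R + (t + s) − 0 = D_R + t + s

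In the first contrast the shared training gain t cancels and only the screen-specific part s remains. In the second nothing cancels.

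**Step 4: can the parts be separated?** Each contrast yields one observed quantity, D_C, and at least two unknowns. Take the Sample size section's target difference of 1.0 point for LSER versus LSE. It is compatible with D_R = 1.0 and s = 0, with D_R = 0.5 and s = 0.5, and with D_R = 0 and s = 1.0. The same holds for the 2.0-point target against control, with t + s in place of s. These are arithmetic possibilities, not estimates. The documents give no value for E, s or t, so the range for the activation share runs from none to all.

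**Step 5: does another stated measure separate them?** No. The outcomes listed are CSA, pain, disability and quality of life. The limitations paragraph says that percentage thickness will not be evaluated and does not mention contraction state.

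**Step 6: does the protocol itself treat activation and structure as distinct?** Yes. The Background describes improved activation as the route by which degenerative changes are believed to be reversed. The endpoint therefore combines the presumed mechanism with the result it is meant to bring about.

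**The case against.** The strongest reply has five parts.

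- **LSE trains the same contraction.** This stands. A reader might infer that only LSER rehearses the measured task; the LSE section contradicts that. For LSER versus LSE the concern is confined to s.
- **The trained and measured tasks are not identical.** This also stands. Training covers L2–L5 and displays thickness, and the contraction is not described as maximal; the outcome is CSA at L5. The overlap is nevertheless substantial, since L5 lies in the trained range and thickness is a dimension of the same cross-section.
- **The size is unknown.** True. One could calculate how often a pure activation gain equal to the target difference would reach significance, but that is only the power for an assumed difference and is not evidence of bias.
- **The hypothesis and primary objective speak only of LMM CSA, the measurement state is disclosed, and the size claim in the Discussion is conditional.** True, so there is no contradiction in the objective. But the condition attached is that the hypothesis is correct, and confirming a hypothesis about contracted CSA would still not establish recovery of size.
- **The procedure is said to match cited studies.** Whether those imaged at rest cannot be checked here. The article is also a condensation, so its silence does not prove that no resting images exist. Precedent would not in any case remove the gap between this endpoint and this conclusion.

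**Conclusion.** The point holds as a limit on interpretation. Contracted CSA is a legitimate outcome and the randomised comparison of it is analysable. What this endpoint alone does not support is the step to recovery of LMM size, or to a causal effect on morphology. LSER versus LSE may include a screen-specific activation gain, and LSER versus control may include the full activation gain; neither can be quantified from the documents.

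Two stronger readings should be resisted. One is that any LSER advantage would be an activation artefact: nothing shows that s or t is large, or even above zero. The other is that resting CSA should now become the primary outcome. Trial status gives first enrolment on August 01, 2019 and follow-up expected to end by September 30, 2021, before the current version was approved on October 4, 2021. On those dates baseline scans cannot be repeated, and changing the primary outcome after data collection would create a problem of its own.

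The verdict rests on the additive split C = R + E, and on no resting measure being available beyond what the article describes.

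**What to change.** 1. In the outcome section and in all reports, define the primary endpoint as *contracted LMM CSA (maximal voluntary isometric contraction)*.
2. In the Discussion, limit the conclusion to contracted CSA. Remove the claims of recovered muscle size and of a causal effect on morphology, and add contraction state to the limitations.
3. If resting images were acquired at the same scans, report resting CSA as a supporting analysis for any structural statement, and leave the primary outcome as it is.

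Items 1 and 2 cost only wording, and item 3 only an additional analysis of existing images. The price is a narrower and less favourable headline conclusion.
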